# Safety and efficacy of camrelizumab combined with radiotherapy as neoadjuvant therapy for locally advanced esophageal squamous cell carcinoma: a prospective single-arm phase II clinical trial protocol

**DOI:** 10.1186/s13063-023-07534-3

**Published:** 2023-08-25

**Keywords:** Esophageal cancer, Neoadjuvant therapy, Immunotherapy, Radiotherapy, Prospective research

## Abstract

**Background:**

Neoadjuvant chemoradiotherapy followed by esophagectomy is the standard of care for locally advanced esophageal squamous cell carcinoma (ESCC). However, approximately 30% of patients still develop distant metastases and have a high incidence of treatment-related adverse events. Immunotherapy, as a new modality for anti-cancer treatment, has shown promising clinical benefits for patients with ESCC. The synergistic effects of immunotherapy and radiotherapy make their combination promising as neoadjuvant treatment for locally advanced ESCC.

**Methods:**

All participants who meet the inclusion criteria will be enrolled after signing the informed consent form. Patients with thoracic segment esophageal cancer with clinical stage T2–3 N0 M0 or T2–3 N + M0 will be included. A total of 25 patients are to be recruited for the study. Twelve patients will be recruited in phase I, with at least two achieving major pathological response (MPR) before entering phase II. They will be treated with radical surgery within 4–8 weeks after the completion of two cycles of neoadjuvant radiotherapy in combination with camrelizumab according to the study schedule. The primary endpoint is the major pathological remission rate of all per-protocol patients. The secondary endpoints are the R0 resection rate, pathological complete remission rate, and adverse events. The interim analysis will be conducted after 12 patients have been enrolled. The trials will be terminated when more than two treatment-related deaths occur or fewer than five patients have major pathological remission.

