### Study design

This prospective study is a single-center, single-arm, prospective phase II clinical study. All participants who meet the inclusion criteria will be enrolled after signing the informed consent form. A total of 25 patients will need to be recruited for the study. Twelve patients will be enrolled in phase I, with at least two patients achieving MPR before entering phase II. The second phase will enroll 13 patients. They will be treated with radical surgery within 4–8 weeks after the completion of two cycles of neoadjuvant radiotherapy in combination with camrelizumab according to the study schedule. The schedule of enrollment, interventions, and assessments is shown in Table 1. If the total number of MPR patients is greater than 7, the results of this study will be considered satisfactory.

**Table 1 Tab1:** Patient assessment schedule

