### Interim analysis and monitoring

We plan to conduct one interim analysis. The interim analysis will be conducted after 12 patients have been enrolled. The Lan-DeMets method with the O’Brien and Fleming type alpha spending function will be used to adjust the multiplicity of the interim analysis [20]. Trials will be terminated when more than two treatment-related deaths occur or there are fewer than two patients with MPR based on the analysis.

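### The abstract stops the trial below five major pathological remissions while the interim section stops it below two, so 2, 3 or 4 of the first 12 is both a stop and a go

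*Protocol article*

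**What the plan says.** The trial enrols 12 patients and then 13 more, 25 in all. The article calls these stages phase I and phase II. Four statements bear on the first-stage decision, which rests on the number of patients with major pathological remission (MPR):

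- Abstract, Methods, entry to the second stage: 12 patients are recruited, "with at least two achieving major pathological response (MPR) before entering phase II".
- Abstract, Methods, termination: after "The interim analysis will be conducted after 12 patients have been enrolled", the next sentence says that the trial is to be "terminated when more than two treatment-related deaths occur or fewer than five patients have major pathological remission".
- Study design, entry to the second stage: 12 patients are enrolled, "with at least two patients achieving MPR before entering phase II".
- Interim analysis and monitoring, termination: the trial ends on more than two treatment-related deaths, or if "there are fewer than two patients with MPR based on the analysis".

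Study design also sets the final criterion: "If the total number of MPR patients is greater than 7, the results of this study will be considered satisfactory". That means at least 8 of 25. The article gives no null rate, target rate or power.

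**The concern.** The two termination sentences are built alike. Each follows the statement that the interim takes place after 12 patients, and each carries the same limit on deaths. They differ only in the MPR count, which is five in the abstract and two in the body. The abstract also disagrees with itself, because its own entry rule lets the trial proceed with two.

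The trial has no control arm and MPR is its primary endpoint, so the credibility of the result leans on decision thresholds fixed in advance. With 2, 3 or 4 remissions, one published sentence ends the trial and three others let 13 more patients be enrolled. A reader of the eventual report could not tell from this article alone whether the decision followed the plan.

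**Working it through.** **1. The statements side by side, for a count X1 among the first 12**

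| X1 | Abstract, termination | Abstract, entry | Study design, entry | Interim section, termination |
|---|---|---|---|---|
| 0–1 | stop | no entry | no entry | stop |
| 2–4 | **stop** | go | go | go |
| 5 or more | go | go | go | go |

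The rules disagree at exactly 2, 3 and 4.

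**2. Could five belong to another time point?** The interim section plans one interim analysis, after 12 patients. The only later decision point is the end, at 25 patients. By then there is nothing left to terminate, and Study design already sets the final bar at more than 7. No section assigns five to any other moment.

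**3. How much the choice matters**

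Inputs from the article: n1 = 12, n2 = 13, N = 25, success at 8 or more. Assumptions: all 12 and all 25 patients are evaluable, and the true MPR rate p is 20%, 30%, 40% or 50%. The plan has no power or error figure to reproduce.

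Formulas, with X1 ~ Bin(12, p), X2 ~ Bin(13, p) and a = the smallest count that continues (2 or 5):

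- P(stop) = P(X1 ≤ a − 1)
- P(rules disagree) = P(2 ≤ X1 ≤ 4)
- P(success) = Σ over x from a to 12 of P(X1 = x) × P(X2 ≥ 8 − x)
- Expected enrolment = 12 + 13 × (1 − P(stop))

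At p = 0.40:

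- P(X1 = 2) = 66 × 0.4² × 0.6¹⁰ = 0.0639
- P(X1 = 3) = 220 × 0.4³ × 0.6⁹ = 0.1419
- P(X1 = 4) = 495 × 0.4⁴ × 0.6⁸ = 0.2128
- The sum, where the rules disagree, is 0.4186.
- P(X1 ≤ 1) = 0.6¹² + 12 × 0.4 × 0.6¹¹ = 0.0022 + 0.0174 = 0.0196, so P(X1 ≤ 4) = 0.0196 + 0.4186 = 0.4382.

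The success that is lost by stopping at 2–4 uses P(X2 ≥ 6) = 0.4256, P(X2 ≥ 5) = 0.6470 and P(X2 ≥ 4) = 0.8314:

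0.0639 × 0.4256 + 0.1419 × 0.6470 + 0.2128 × 0.8314 = 0.296

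This equals 0.8423 − 0.5463, the difference between the two success probabilities at 40%.

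| True rate | P(stop), below two | P(stop), below five | P(rules disagree) | P(success), below two | P(success), below five | Expected N, below two | Expected N, below five |
|---|---|---|---|---|---|---|---|
| 20% | 0.275 | 0.927 | 0.653 | 0.108 | 0.042 | 21.4 | 12.9 |
| 30% | 0.085 | 0.724 | 0.639 | 0.484 | 0.239 | 23.9 | 15.6 |
| 40% | 0.020 | 0.438 | 0.419 | 0.842 | 0.546 | 24.7 | 19.3 |
| 50% | 0.003 | 0.194 | 0.191 | 0.977 | 0.804 | 25.0 | 22.5 |

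**4. Can the design itself tell which number was meant?** Not from the article. As a side check on assumed inputs, a Simon optimal design with null rate 20%, target rate 40%, one-sided alpha 0.10 and power 0.80 gives 12 then 13 patients and success above 7 of 25. It stops at 2 or fewer of 12, which matches neither printed number. The article does not state these inputs, so the check shows only that the sizes and the final bar do not point uniquely to two or to five.

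**The case against.** The strongest reply is that this is a slip in an abstract. Three of the four statements use two, including both body sections, and the abstract's termination sentence does not itself say that it applies at the interim. That stands as a likely explanation. It does not remove the conflict, because both numbers are printed as current text and nothing in the article says which prevails.

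A reader might also infer more than the article supports:

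- **That the operating characteristics are undefined.** They are not. Study design and the interim section together give a complete rule (12 then 13, go at two, success above 7), and its properties follow for any assumed rate.
- **That fewer than five of 25 would contradict the final criterion.** It would not. Below five could count as failure and above 7 as satisfactory, with 5 to 7 in between. The final reading fails for the reasons in step 2 of the working, not on logic.
- **That five of 12 cannot coexist with 8 of 25.** Five of 12 (5/12 = 41.7%) is stricter than 8 of 25 (8/25 = 32%) and costs a good deal of power, but a stricter first stage is possible.
- **That this is the only efficacy rule at the interim.** The interim section also names a Lan-DeMets alpha spending function of O'Brien-Fleming type, without giving its boundary. The count discussed here is the only stated MPR count for stopping.

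Finally, the probabilities treat every enrolled patient as evaluable. The primary endpoint is per protocol, and surgery depends on there being no metastatic disease, so the evaluable numbers may be smaller and the figures would shift.

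**Conclusion.** The stopping rule is wrong as written: the article prints two different first-stage MPR thresholds for the same interim. The conflict at 2, 3 and 4 of 12 follows from the text alone and needs no assumption. Its size depends on assumed true rates and full evaluability. Over rates of 20% to 50%, the probability of landing in the disputed range runs from 0.65 down to 0.19. At 40%, the chance of stopping is 0.02 or 0.44, and the chance of reaching 8 of 25 is 0.84 or 0.55, depending on which sentence is followed.

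The majority of statements makes two the more likely intention, and a reader might conclude that five should simply be struck. The article does not justify that step, because it gives no null rate, target rate or power to confirm either number.

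**What to change.** Take the first-stage MPR boundary from the sponsor's two-stage design calculation and state that one number in the abstract, Study design, and Interim analysis and monitoring. Document that this boundary was in force before the first-stage pathology was read. If the interim has already taken place, report the observed MPR count and the rule that was applied. The cost is an erratum, with no added patients or procedures.

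### The abstract stops the trial at the 12-patient interim for fewer than five MPRs, while every other statement of the rule uses two, so 2, 3 or 4 MPRs calls for both stopping and continuing

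*Protocol article*

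**What the plan says.** The Protocol article states the stage 1 MPR rule four times.

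- Abstract, Methods, opening of the second stage: "Twelve patients will be recruited in phase I, with at least two achieving major pathological response (MPR) before entering phase II".
- Abstract, Methods, stopping rule: directly after the sentence "The interim analysis will be conducted after 12 patients have been enrolled", the trial is to end when "more than two treatment-related deaths occur or fewer than five patients have major pathological remission".
- Study design: "Twelve patients will be enrolled in phase I, with at least two patients achieving MPR before entering phase II".
- Interim analysis and monitoring: the same look after 12 patients and the same death criterion, but the MPR condition for termination is that "there are fewer than two patients with MPR based on the analysis".

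The last section also says "We plan to conduct one interim analysis". Study design sets the final criterion at more than 7 MPRs in 25 patients, 12 in the first stage and 13 in the second.

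**The concern.** One decision has two boundaries. A count of 0 or 1 stops the trial under all four statements, and 5 or more lets it continue under all four. A count of 2, 3 or 4 stops it under the abstract's last sentence and continues it under the other three. In a single-arm study the MPR count is likely to be known when the decision is taken, and either decision could then be defended from the published text. The two boundaries give very different probabilities of early stopping and of a successful final result, so the article does not fix the design's operating characteristics.

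**Working it through.** **Can the statements be read together?**

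1. As a rule for the final analysis, fewer than five does not fit: Study design already requires more than 7 of 25.
2. As a rule for another look, it does not fit: only one interim analysis is planned.
3. The abstract's stopping sentence follows the interim sentence directly and carries the same death criterion as the Interim analysis and monitoring section. It is the same rule with a different number.

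**Inputs.** From the article: 12 patients at the interim, 25 in total (13 in stage 2), success if total MPRs are at least 8. The article gives no null rate, target rate or power, so no stated boundary can be reproduced. The true MPR rate p is therefore an assumed range, and 12 evaluable patients are assumed at the interim.

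**Formulas.** X is binomial(12, p) and Y is binomial(13, p), independent.

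- Stop if fewer than two: P(X ≤ 1) = (1−p)^12 + 12p(1−p)^11.
- Conflict zone: P(2 ≤ X ≤ 4) = 66p²(1−p)^10 + 220p³(1−p)^9 + 495p⁴(1−p)^8.
- Stop if fewer than five: P(X ≤ 4), the sum of the two lines above.
- Final success: the sum over x = a to 12 of P(X = x) · P(Y ≥ 8 − x), with a = 2 or a = 5.

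**Worked case, p = 0.40.** P(X ≤ 1) = 0.0022 + 0.0174 = 0.0196. P(2 ≤ X ≤ 4) = 0.0639 + 0.1419 + 0.2128 = 0.4186. P(X ≤ 4) = 0.0196 + 0.4186 = 0.4382.

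**Results (exact binomial).**

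| Assumed true MPR rate | P(2, 3 or 4 of 12) | P(stop), fewer than 2 | P(stop), fewer than 5 | P(success), fewer than 2 | P(success), fewer than 5 |
|---|---|---|---|---|---|
| 20% | 0.653 | 0.275 | 0.927 | 0.108 | 0.042 |
| 30% | 0.639 | 0.085 | 0.724 | 0.484 | 0.239 |
| 40% | 0.419 | 0.020 | 0.438 | 0.842 | 0.546 |
| 50% | 0.191 | 0.003 | 0.194 | 0.977 | 0.804 |
| 60% | 0.057 | 0.0003 | 0.057 | 0.999 | 0.943 |

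At 40% the choice of boundary changes the chance of success by 0.842 − 0.546 = 0.296.

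**False positives.** With no interim look, P(at least 8 of 25) at a true rate of 20% is 0.109. The boundary of two lowers it to 0.108 and the boundary of five to 0.042. Any choice between the two, even one made after seeing the count, cannot exceed the 0.108 of the more lenient rule.

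**The case against.** The best case on the other side is that the ambiguity is narrow. Both sections of the main text and the abstract's own earlier sentence agree on two, and the outlier is one sentence of the abstract. That stands, and it makes five the probable slip. It does not settle the matter, because the article prints no design inputs from which either number can be confirmed.

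The size is also sensitive to the assumed rate. The article quotes pathological complete remission rates of 39.2%, 43.2% and 55.6% in squamous disease. Those regimens included chemotherapy, so they are not direct anchors. But MPR as defined includes complete remission, so rates above 40% belong in the range, and there the conflict zone shrinks to 0.19 at 50% and 0.06 at 60%. The figures further assume 12 evaluable patients, whereas the look follows 12 enrolled and the endpoint is per-protocol. These limits stand.

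Three stronger readings are tempting, and the article does not support them:

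- **The boundary of two is itself off by one.** An optimal two-stage design for 20% against 40%, one-sided alpha 0.10 and power 0.80 has 12 and 25 patients and a final cut-off of more than 7, and it stops at 2 or fewer. None of those inputs is in the article, whose Statistical analysis section gives 0.05, and no such design is named. The printed rule with two is workable at 0.05: for an assumed null of 15% and target of 40%, its type I error is 0.025 and its power 0.842.
- **Error control is lost.** Both boundaries are futility rules and can only lower the false-positive rate.
- **Stage 1 has no other stopping rule.** More than two treatment-related deaths also ends the trial, in both places where termination is described.

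**Conclusion.** Wrong as written. The abstract's stopping sentence contradicts its own earlier sentence, the Study design section and the Interim analysis and monitoring section. The contradiction needs no assumption; only its size does. For assumed true rates of 20% to 30% an interim count on which the rules disagree is more likely than not (0.653 and 0.639). It is still a substantial possibility at 40% (0.419) and becomes unlikely by 60% (0.057). The consequence lies in power and in the chance of early stopping. The article does not show which number the design used, although the count of three statements to one points to two.

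**What to change.** Reconcile the abstract with Study design and with Interim analysis and monitoring against the original sample-size calculation. Print one MPR boundary in all three places, and state the null rate, target rate, alpha, power and early-stopping probability that go with it. If the calculation confirms two, only the abstract's last Methods sentence needs a new number; if it gives another value, all the statements must change.

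Inclusion began in February 2022 and the article appeared in August 2023, so the interim may already have taken place. In that case, report which rule was applied and the MPR count on which the decision was made.

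The cost is a wording correction and a correction notice. No extra patients are needed.

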**Discussion:**

We designed this prospective single-arm phase II clinical study to evaluate the combination of camrelizumab and standard radiotherapy as preoperative neoadjuvant therapy for patients with resectable ESCC as part of the quest for better treatment options for patients with locally advanced ESCC.

**Trial registration:**

This trial protocol has been registered on the NIH Clinical Trials database (www.clinicaltrials.gov/, NCT05176002. Registered on 2022/01/04). The posted information will be updated as needed to reflect protocol amendments and study progress.

## Background

Esophageal cancer is the seventh most common cancer and the sixth most common cause of cancer-related death globally [1]. Its most prevalent pathological type is esophageal squamous cell carcinoma (ESCC), which accounts for more than 90% of cases globally, and China is among the regions with the highest risk [2]. The National Comprehensive Cancer Network and Chinese Society of Clinical Oncology guidelines recommend neoadjuvant radiotherapy followed by esophagectomy as the standard of care for locally advanced ESCC [3]. However, the CROSS and NEOCRTEC5010 studies reported a high incidence of distant metastases after neoadjuvant chemoradiotherapy at 39% and 23.9%, respectively [4, 5]. Therefore, a more effective systemic antitumor regimen is the next priority for the comprehensive treatment of ESCC.

In recent years, immunotherapy has demonstrated clinical benefits as a new treatment regimen for patients with locally advanced and metastatic ESCCs [6, 7]. The PALACE-1 study reported that 20 cases of locally advanced ESCC were treated with neoadjuvant chemoradiotherapy combined with immunotherapy, and surgery was successful for 18 cases; only one case of tumor progression and another case of death during treatment were reported. The pathological complete remission (pCR) rate was 55.6%, which was higher than those reported by the NEOCRTEC5010 and CROSS studies. However, a higher prevalence of treatment-related adverse events (AEs) was also reported, with grade III or higher AEs observed in 65% of patients [8]. Li et al. showed that 60 patients with locally advanced ESCC received neoadjuvant camrelizumab immunotherapy in combination with chemotherapy, and 51 received neoadjuvant therapy and underwent surgery successfully. The pCR rate was 39.2%, and the most common treatment-related AE was leukopenia (86.7%). Thirty-four patients (56.7%) had grade 3 or worse AEs [9]. The treatment-related AEs predominantly involved the hematologic and digestive systems, both of which are commonly involved in AEs of chemotherapy [8, 9].

Some studies have suggested that conventional radiation therapy is effective by promoting systemic anti-tumor immunity, thereby reducing the risk of recurrence and improving patient survival [10]. For other types of malignancies, immunotherapy combined with radiotherapy has demonstrated significantly better efficacy with an acceptable incidence of AEs [11, 12]. Relevant preclinical studies have shown that the effects of radiotherapy and immunotherapy are synergistic, rather than simply cumulative [13, 14]. Immunotherapy has been reported to increase radiosensitivity in patients with ESCC, resulting in effective control of local lesions and distant micrometastases, while radiotherapy can enhance the effect of immunotherapeutic agents by upregulating PD-L1 expression in the tumor microenvironment [15, 16]. To further evaluate the prospects of immunotherapy combined with radiotherapy as neoadjuvant treatment for patients with locally advanced ESCC, we designed this single-center, single-arm, prospective phase 2 clinical study as part of the quest for practical, novel therapeutic options for neoadjuvant locally advanced ESCC.

## Methods/design

### Study objectives

The primary objective of this study is to assess the safety of camrelizumab combined with standard radiotherapy as preoperative neoadjuvant therapy for patients with locally advanced ESCC, and the secondary objective is to assess the efficacy of the neoadjuvant therapy. The present study also aims to explore the biomarkers and the quality of life in patients with locally advanced ESCC.

### Study design

This prospective study is a single-center, single-arm, prospective phase II clinical study. All participants who meet the inclusion criteria will be enrolled after signing the informed consent form. A total of 25 patients will need to be recruited for the study. Twelve patients will be enrolled in phase I, with at least two patients achieving MPR before entering phase II. The second phase will enroll 13 patients. They will be treated with radical surgery within 4–8 weeks after the completion of two cycles of neoadjuvant radiotherapy in combination with camrelizumab according to the study schedule. The schedule of enrollment, interventions, and assessments is shown in Table 1. If the total number of MPR patients is greater than 7, the results of this study will be considered satisfactory.

**Table 1 Tab1:** Patient assessment schedule

	**Study period**									
**Timepoint**	**Enrolment**	**Combined therapy** **Camrelizumab + Radiation**		**Surgery**	***Follow-up after surgery***					**Close-out**
	***0***	**Cycle 1**	**Cycle 2**	***1 week***	***4 weeks***	***12 weeks***		***Every 6 months***		***t***_***x***_
**Enrolment:**										
**Eligibility screen**	X									
**Informed consent**	X									
***Assessments:***										
**Baseline patient characteristics**	X									
**Baseline tumor characteristics**	X									
***Laboratory examination***	X	X	X							
***Tumor response evaluation***		X	X							
***Postoperative outcome data***				X						
***pathological assessment***				X						
***Adverse events assessment***		X	X	X	X		X		X	
***Quality of life measure***					X		X		X	X
***Survival***					X		X		X	X

